#### Patients

We will enroll patients 60 years of age or older with one or more of the following conditions: diabetes, hypertension and history of cardiac disease (heart failure and myocardial infarction). Exclusion criteria include: mini-mental state examination (MMSE) [20] score < 24, inability to complete the research tasks, history of any form of atrial fibrillation, history of using warfarin (but not of using aspirin or any other anti-platelet agent since their use is ubiquitous in the target population), inability to participate because of illness, or unavailability.

Patients with newly diagnosed atrial fibrillation who are contemplating the choice of antithrombotic therapy to prevent strokes represent the ideal patient population. There are, however, logistical challenges in prospectively identifying such a group and in ensuring their participation prior to their making a decision about using or not using antithrombotic therapy. Not enrolling patients after they have made a decision regarding anticoagulation is crucial to prevent bias as a result of cognitive dissonance. Cognitive dissonance (a state of psychological discomfort due to inconsistent cognitions) could readily lead patients to modify their interpretation of information provided during the study to ensure it was consistent with their previous decision, a decision that may or may not have been well-informed [21].

The next best choice is to enroll patients at high risk of developing atrial fibrillation who may have to make this choice in the near future. This proximity to the choice increases the likelihood that patients will view the exercise as relevant to them and we will obtain meaningful responses that are reflective of the patients' true preferences. Thus, the eligible patient will be at high risk of atrial fibrillation according to data from the Framingham study [6]. This study identified the following risk factors for atrial fibrillation: age, hypertension, diabetes, history of cardiovascular disease, valvular heart disease, and heart failure. These inclusion and exclusion criteria are broader than but consistent with eligibility criteria used in our previous work in which we recruited patients with previous myocardial infarction or heart failure [12].

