Our study should be powered to determine differences in means of *b*_*p *_and *b*_*c*_, that is, differences in the treatment preferences of patients and clinicians, the key variable. In our previous study, the effect size (difference in mean *b *between patients and clinicians) was 0.9 (this is calculated from sample means (and SDs) of 2.2 (0.9) and 1.3 (0.8) in the patients and clinicians, respectively). Although it is not immediately evident what magnitude of the difference in *b *would be clinically important, readers and commentators have uniformly considered the differences we showed as important. Table 2 shows the power we would have with the proposed sample size of 96 clinicians and an equal number of patients, and also illustrates the limited impact of increasing the number of patients from 1:1 to 1:3. Therefore, given the number of clinicians available to us, we will have ≥ 80% power to detect differences in means ≥ 0.4·SD. We will have ≥ 80% power to detect differences in means of *b*_*p *_and *b*_*c *_≥ 0.75·SD between subgroups of ≥ 20 clinicians and 96 patients. In summary, after enrolling 96 patients and 96 clinicians we will have ≥ 80% power to detect (1) *b*_*p *_- *b*_*c *_> 0.4 SD, (2) odds ratio ≥ 2.6 of the proportion of patients and clinicians with *b *> *b*_*RCT *_(if that proportion is 0.63 or smaller among clinicians), and (3) a difference in mean utilities of ≥ 0.4 SD. We need to enroll 96 clinicians to ensure 8 members per focus group. Enrolling more than 96 patients has a very small impact on power. Thus, we will recruit 96 patients and 96 clinicians for this study.

**Table 2 T2:** Power to detect differences in means of *b*_*p *_and *b*_*c *_0.2 to 0.5 standard deviation units (α = 0.05)

** *Sample* **		*b*_*p *_- *b*_*c *_difference in SD units			
Clinicians	Patients	0.2	0.3	0.4	0.5
96	96	.28	.54	.79	.93
96	144	.33	.62	.86	.97
96	192	.36	.67	.89	.98
96	288	.39	,71	.92	.99

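### The drug-history exclusion names only past warfarin use and is narrower than the plan's concern about earlier anticoagulation decisions, so some patients with such a decision for another indication stay eligible (minor)

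*Protocol article*

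**What the plan says.** The Patients section of the protocol article lists, one after the other, two exclusions that bear on earlier treatment decisions: "history of any form of atrial fibrillation, history of using warfarin (but not of using aspirin or any other anti-platelet agent". The article admits anti-platelet users because these drugs are taken so widely. No other anticoagulant is named, and nor is a refused offer of treatment.

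The next paragraph explains why newly diagnosed patients, though ideal, are not sampled. It mentions the difficulty of "ensuring their participation prior to their making a decision about using or not using antithrombotic therapy" and then states: "Not enrolling patients after they have made a decision regarding anticoagulation is crucial to prevent bias as a result of cognitive dissonance". The solution it adopts is introduced with the words "The next best choice is to enroll patients at high risk of developing atrial fibrillation who may have to make this choice in the near", meaning people who have yet to face the decision. Eligible patients are 60 or older with at least one of "diabetes, hypertension and history of cardiac disease (heart failure and myocardial infarction".

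Under Recruitment strategy, each site supplies a random sample of eligible patients, and the study coordinator confirms eligibility by telephone. Sample size estimation sets the numbers: "Thus, we will recruit 96 patients and 96 clinicians for this study".

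**The concern.** The plan's argument is about having already decided. Someone who has chosen for or against anticoagulation may read the study's scenarios so that they fit that choice. The argument does not depend on which drug was involved, and the decision described includes deciding not to treat. The drug-history criterion screens for one drug, and for use only.

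Two groups without atrial fibrillation therefore pass: those who took another oral anticoagulant, and those who were offered one and declined. Among people offered warfarin for another indication, those who took it are removed and those who refused are kept.

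These patients' answers enter three comparisons with clinicians: the mean of b and the proportion choosing warfarin at b_RCT (both Research question 2), and the utility for taking warfarin (Research question 3).

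**Working it through.** **Who is removed by the rules as written**

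- Atrial fibrillation, took or declined any anticoagulant: removed by the atrial fibrillation exclusion.
- No atrial fibrillation, took warfarin: removed by the warfarin exclusion.
- No atrial fibrillation, took a different oral anticoagulant: not removed.
- No atrial fibrillation, offered an anticoagulant and declined: not removed.

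The second line shows what the warfarin criterion adds. With atrial fibrillation already excluded, the only further people it can remove are those who took warfarin for some other reason. The plan therefore already treats exposure for other indications as disqualifying, but only for one drug. The parenthesis in that criterion permits anti-platelet drugs explicitly; anticoagulants other than warfarin are neither permitted nor excluded.

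**Inputs for the size**

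- Patients and clinicians: 96 each (Sample size estimation).
- Detectable difference: 0.4 SD. Table 2 gives power .79 for 96 v 96 at this difference; recalculation gives 0.791, so the benchmark reproduces.
- Share of enrolled patients in the gap, f: not in the article. Assumed 1% to 10%, which is 96 × 0.01 = 0.96 to 96 × 0.10 = 9.6 patients.
- Difference in b between these patients and the rest, s: not in the article. Assumed 0.5 to 1.0 SD, all in one direction.

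**Formula:** shift in the patient mean of b = f × s, in SD units; relative size = shift / 0.4.

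| f | s = 0.5 SD | s = 1.0 SD |
|---|---|---|
| 1% | 0.005 SD (1.25% of 0.4) | 0.01 SD (2.5%) |
| 5% | 0.025 SD (6.25%) | 0.05 SD (12.5%) |
| 10% | 0.05 SD (12.5%) | 0.10 SD (25%) |

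On the scale of the previous study, where the patient SD of b was 0.9, the largest entry is 0.10 × 0.9 = 0.09. The difference between patients and clinicians found there was 2.2 − 1.3 = 0.9, so the largest entry is a tenth of it.

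**Direction.** By the plan's own argument, patients who refused would lean towards refusal and lower the patient mean of b. Former users of another anticoagulant could move it either way, so the two groups may partly cancel. The plan expects patients to have the higher b, so a downward shift would shrink the expected difference.

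**The case against.** The strongest reply is that the decision the study elicits is already protected. It concerns warfarin or aspirin for atrial fibrillation, and anyone with a history of that condition is out, whatever they took or refused. A reader might infer from the warfarin wording that everyone who used another anticoagulant or declined one remains in the sample. The text does not support that: only decisions made for other indications remain. This part of the reply stands and sets the limit of the point.

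Second, the article gives no reason for the warfarin criterion. The cognitive dissonance sentence belongs to the discussion of newly diagnosed patients, so it cannot be called the stated reason for that criterion. This also stands. It does not remove the mismatch, because the warfarin criterion can act only on people treated for something other than atrial fibrillation, and the article does not say why one drug should count and another not.

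Third, the list is introduced as a non-exhaustive one in a condensed article, so fuller wording may exist elsewhere. That is possible. The rule as printed, however, does not tell whoever draws the sample or makes the eligibility call to ask about other anticoagulants.

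Fourth, the documents do not show that refusing treatment for another disease affects choices about stroke prevention in atrial fibrillation. This is a fair doubt. It makes declined offers a weaker case than past use of another anticoagulant.

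A reader might also take the extreme corner of the table, a 0.10 SD shift, and report a t test false-positive rate of 10.6% instead of 5%. That needs the largest assumed share, the largest assumed shift and every affected patient moving the same way, so it is not a fair summary. Nor does the article describe local prescribing, so nothing can be concluded about how many people the warfarin wording would actually catch.

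**Conclusion.** The mismatch can be read directly from the Patients section: the drug-history criterion is narrower than the plan's own concern about earlier decisions, and followed as written it admits some patients with a prior anticoagulation decision for a non-atrial-fibrillation indication. A biased comparison is not demonstrated. The number of such patients is not given, and both the assumed share (1% to 10%) and the assumed shift (0.5 to 1 SD) are mine. On those assumptions the patient mean of b moves by 0.005 to 0.10 SD, at most a quarter of the 0.4 SD detectable difference, with uncertain direction. The effect on the proportion at b_RCT and on the utility for taking warfarin cannot be sized from the article. The point is minor and worth making because it is cheap to close.

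**What to change.** In the Patients section, widen the drug-history exclusion from past use of warfarin to past use of any oral anticoagulant, preferably adding people who were offered one and declined. Keep the allowance for aspirin and other anti-platelet drugs. Add the matching question to the coordinator's eligibility call under Recruitment strategy. If the investigators consider that only decisions made for atrial fibrillation matter, they could say so instead and explain why the separate warfarin criterion is kept.

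The cost is one line in the criteria and one question in a call that is already planned. A few more patients would be screened out and replaced from the sites' random samples; the target of 96 patients and the analysis do not change.

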#### Recruitment strategy

We will use several strategies to recruit patients and clinicians for this study. In the case of patients we will sample them from the different databases of the Health Areas from the three sites where the study will take place. Each site will provide a random sample of patients fulfilling eligibility criteria for participation. We will invite these patients to participate initially with a phonecall from their primary care physician or a delegate from their center. The study coordinator will follow-up with a phone call to verify eligibility, obtain verbal consent, and set up an interview date. Patients will give written informed consent to participate.

We will sample practicing clinicians working in general medicine (primary care, family medicine, internal medicine) and in cardiology, based in the community or in the hospitals. Clinicians who spend less than 30% of their time seeing patients in the outpatient or inpatient settings or if they have not cared for a patient with atrial fibrillation in the preceding six months are ineligible to participate. These eligibility and exclusion criteria should select clinicians who participate in making decisions about antithrombotic therapy with patients with atrial fibrillation, the most relevant group for our study. We will send an electronic letter to clinicians inviting them to participate in this study. A second mailing will follow if the local investigator receives no answer. Finally, clinicians who have not responded to the 2 mailings will receive a phone call from the local study investigator (a local colleague) inviting them to enroll.

In our experience, time is the main barrier to clinician participation. We plan to complete each clinician interview within 30 minutes. To achieve this goal, we will use a highly scripted interview with extreme economy of items. To ensure the success of the focus groups, we will use multiple ways to get clinicians to the focus group venue on time. These include, but are not limited to, sending periodic e-mail reminders, contacting their administrative assistants to include the focus group on their daily calendars, making same-day reminder phone calls, and arranging for transportation to the focus group venue, as needed.

### First phase: the individual interview

The clinical context of this decision study is the use of antithrombotic agents to treat chronic non-valvular atrial fibrillation. Both patients and clinicians will go through an individual highly scripted interview. To determine their strength of preference for use of antithrombotic agents we will conduct a probability trade-off exercise. This will answer the first research question and will allow us to determine if there is a difference and if present the magnitude of the difference in strength of preference for treatment between patients and clinicians, the second research question.

To partially answer the third research question (whether differences in utilities for the relevant health states explain differences in treatment preferences) we will ask participants to assign relative value to the relevant health states using a visual analog scale (also known as the feeling thermometer). The complete elicitation of treatment preferences and utilities will take approximately 15 minutes. The patients will receive the mini-mental state examination and 2 additional "screening" scenarios to gauge their ability to participate in the probability trade-off exercise. Thus, we expect patient interviews to take 45 minutes and clinician interviews to take 30 minutes to complete.

To account for order effects, we will randomize the order in which participants complete the exercises (probability trade-off and feeling thermometer) and the health states within the feeling thermometer (mild stroke, major stroke, taking warfarin, taking aspirin, severe bleeding). Clinicians could answer questions thinking about what they would choose for themselves (if they were to have atrial fibrillation) or what they would recommend to their patients. To eliminate this ambiguity (and study this potential effect), and following the method by Cohen and Pauker [22], we will randomize clinicians to instructions that ask them to participate and complete the preference elicitation tasks in the role of a patient or as a clinician making a recommendation to a patient.

Prior to the preferences elicitation exercises, patients will complete a brief questionnaire indicating their age and gender and whether they have personal knowledge of someone who had a major or a minor stroke, or a major gastrointestinal bleed. Likewise, clinicians will indicate their demographic characteristics, the number of years in practice, specialty, and experience with atrial fibrillation, bleeds and strokes.

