**Figure 2 F2:**
[figure not shown]
**Section of the decision board for probability trade-off**[1]**comparing outcomes of****2 years of warfarin use****vs. aspirin among 100 patients with atrial fibrillation, as used in our preliminary study**[12].

During the individual interview, we will present complete information about the risks, benefits, and inconveniences of warfarin and aspirin. To demonstrate how we will determine a patient's threshold for accepting a treatment we will discuss the scenario for determining the maximum bleeding increase acceptable for warfarin therapy (i.e. the bleeding threshold for warfarin) in a comparision of warfarin vs. aspirin.

The scenario is based on the absolute effects of both drugs on 100 patients over a two-year period. We will use a probability trade-off with the elicitation method of "ping-ponging" to determine participant's thresholds. The interviewer will systematically vary the risk of bleeding with warfarin (alternating between high and low risk of bleeding) to determine the maximum acceptable increase in the risk of bleeding with warfarin, given a fixed reduction in the risk of stroke with warfarin relative to a fixed risk of bleeding and stroke with aspirin. The alternating presentation of high and low risk of bleeding may reduce "start point bias" resulting from starting the exercise at the point of known efficacy and safety of the medications.

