The decision boards will reflect the best available evidence, namely from the meta-analysis of warfarin vs. aspirin for atrial fibrillation [11] (Table 1). Our scenario will start with a statement of the baseline risk–"with aspirin treatment there is a baseline risk of a major or minor stroke over the next two years of 8 patients out of 100 and a risk of severe bleeding over the next two years of two patients out of 100. In the case of warfarin there is a baseline risk of major or minor stroke over the next two years of 5 patients out of 100". We will then present that risk of bleeding using a flipchart. In this first flipchart we will start randomly with either no additional bleedings or with up to 17 additional bleeds. If the participant decides that she would still take warfarin with 17 additional bleeds, with the help of a second flipchart, we will offer up to 38 additional bleeds (starting either at 18 additional bleeds or at 38 and using the same "ping-ponging" method). In the case of a patient or physician accepting the 38 additional bleeds we will ask her what is the maximum number of bleeds she would accept before switching to aspirin.

**Table 1 T1:** Summary of results of meta-analysis of warfarin vs. aspirin in patients with atrial fibrillation [11]

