#### The feeling thermometer

To further understand the treatment preferences elicited using the probability trade-off and capture the values patients and clinicians place on the health states that may result from their choice, namely strokes and bleeds, we will conduct preference-elicitation exercises using the feeling thermometer, a visual analogue scale [27,28]. When completing the feeling thermometer patients choose the score on the thermometer that represents the value they place on the health state they are being asked to evaluate. The feeling thermometer is anchored at death (0) and perfect health (100). The feeling thermometer will allow us to check understanding of the relative severity of the health states in question (i.e., patients should assign a lower value (a value closer to 0) to a major stroke with severe and permanent disability than a minor stroke).

Because the visual analogue scales may be prone to context bias, that is rating of one state may influence rating of other states [29,30], we will randomize the order in which participants will consider the health states to minimize this bias. We will ask participants to consider the following health states one at a time on the feeling thermometer:

▪ Major and minor strokes. We will inform patients that the sequelae of the stroke will last for the patient's life expectancy.

▪ Severe bleed. We will inform patients that they will have a major bleed within the first year of taking the antithrombotic agent but will not have another severe bleeding event for the rest of their life

▪ Taking warfarin

▪ Taking aspirin

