##### Description of treatment preferences

We will use probability trade-off results to determine the number of additional bleeds that participants are willing to tolerate per stroke prevented with warfarin at the point of switch to aspirin. We will call this variable *b*. We will describe the distribution of *b *in clinicians grouped by age, gender, years in practice, specialty, experience with atrial fibrillation, experience with bleeds and strokes, and whether they participated as clinicians or as patients. We will also describe *b *in patients grouped by age and gender, and by personal knowledge of someone who had a major or a minor stroke, or a major gastrointestinal bleed. We will also describe the distribution of *b *in clinicians and patients by site. We will conduct exploratory linear regression analysis using *b *as the dependent variable and clinician characteristics listed above as the independent variables. The results of this analysis will guide our choices for subgroup analyses to answer Research Question 2.

#### Research question 2

To what extent do patients' and clinicians' treatment preferences differ?

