##### Differences in treatment preferences between patients and clinicians

We will test the difference of the means of *b *between the patients (*b*_*p*_) and clinicians (*b*_*c*_) using an unpaired *t *test. The observed distribution of *b*_*p *_in our preliminary work was highly skewed. This was because patients clustered at the highest *b *offered. For this study, we propose to offer a maximum *b *that is twice as large as the maximum *b *offered in our preliminary study. Furthermore, we will be studying a relatively large number of patients and clinicians with distribution of the means approximating the normal distribution with SEM = SD/vn. Our sample sizes will be considerably larger than 30, a size which is often taken as a guideline threshold, above which the sample distribution of the sample mean will be reasonably normally distributed, even if the distribution of individual values is substantially skewed. Thus, the use of the t-test is appropriate. However, we will also use the Mann-Whitney test, a non-parametric test that does not require the assumption of normality of the distribution. After identifying pertinent subgroups in the analysis to Research Question 1, we will conduct modified *t *tests to test the difference of the means of *b *between the patients and the subgroup of clinicians of interest. A modified *t *test is based on the pooled estimate of variance from all the subgroups [33]. The resulting *P *values can be adjusted for multiple comparisons using the Bonferroni method (multiplying the resulting *P *value by the number of paired comparisons performed).

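### Exercise order and first-flipchart start are randomised but enter no stated analysis; adding them as model terms would gain modest precision at almost no cost

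*Protocol article*

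**What the plan says.** Under the heading for the individual interview, the protocol article states: "To account for order effects, we will randomize the order in which participants complete the exercises". The same sentence covers the order of health states within the feeling thermometer, and the thermometer section repeats the aim: "we will randomize the order in which participants will consider the health states to minimize this bias".

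For the probability trade-off, the article names start-point bias and offers a procedural remedy: "The alternating presentation of high and low risk of bleeding may reduce" it. It then adds a random start: "In this first flipchart we will start randomly with either no additional bleedings or with up to 17 additional bleeds". Participants who still accept warfarin at 17 move to a second flipchart, "starting either at 18 additional bleeds or at 38 and using the same" alternating method. The article does not say that this second start is random.

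The analysis plan for research question 2 reads "We will test the difference of the means of" *b* between patients and clinicians, by unpaired *t* test, with a Mann-Whitney test alongside and Fisher's exact test for the proportions at the trial-based value of *b*. For research question 3, utilities are compared by Mann-Whitney and *t* tests, and *b* is correlated with and regressed on the utilities.

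The exploratory regression under research question 1 uses the "clinician characteristics listed above as the independent variables". That list ends with "experience with bleeds and strokes, and whether they participated as clinicians or as patients", so the randomised clinician role is included. Exercise order and starting point appear in none of these analyses.

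**The concern.** The article regards order and starting point as capable of moving responses, which is why it randomises them. A randomised two-level factor that shifts *b* adds to the spread of *b*. Randomising balances it between patients and clinicians on average, but its variance stays in the error term unless the model contains the factor.

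Three things are at stake, all modest:

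- Precision in the main comparison, where the number of clinicians is limited by availability.
- Interpretation under research question 3. If doing one exercise first shifts both *b* and a utility, exercise order is a common cause of the two, and their correlation partly reflects the interview procedure. Randomising order does not remove this from an analysis that pools the two orders.
- Information. The study aims to rule out alternative explanations of the earlier result, and the stated analyses would not show whether thresholds depend on where the flipchart began.

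**Working it through.** **Inputs from the article.** 96 clinicians and 96 patients; α = 0.05; power .79 at 0.4 SD (Table 2); earlier means (SD) of *b* of 2.2 (0.9) in patients and 1.3 (0.8) in clinicians (sample size section).

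**Assumptions.** Two-sided testing, 1:1 allocation to each order and start, additive effects, and no interaction with group. The article gives no size for an order or starting-point effect, so a range is shown.

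**1. Reproduce the plan's figure.** In SD units the standard error of the group difference is √(2/96) = 0.144. Power at 0.4 SD is Φ(0.4/0.1443 − 1.96) = Φ(0.811) = 0.791, or 0.787 with the noncentral *t*. Table 2 gives .79, and its other cells reproduce as well. The unit is the total SD, which already contains any variance due to order or start.

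**2. Variance due to one factor.** A 1:1 factor that shifts *b* by *d* total SDs has variance *d*²/4. After adjustment the SD is √(1 − *d*²/4), and power at 0.4 SD is:

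| Assumed *d* | Share of variance | SE after adjustment | Power, normal | Power, noncentral *t* |
|---|---|---|---|---|
| none | 0 | 0.144 | 0.791 | 0.787 |
| 0.2 | 0.010 | 0.144 | 0.795 | 0.791 |
| 0.3 | 0.0225 | 0.143 | 0.800 | 0.796 |
| 0.5 | 0.0625 | 0.140 | 0.817 | 0.813 |
| 0.8 | 0.160 | 0.132 | 0.856 | 0.853 |

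Two factors of 0.5 SD each would give 0.842.

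**3. Chance imbalance.** Under simple randomisation, the between-group difference in the share starting high has SD √(2 × 0.25/96) = 0.072. At *d* = 0.5 it contributes an SD of 0.5 × 0.072 = 0.036 to the group difference. Its variance is 0.036² = 0.0013, against 0.144² = 0.0208 in total: the same 6% as in the table. It is part of the unadjusted standard error and does not come on top of it.

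**4. Validity of the unadjusted test.** Simulation with two unmodelled factors (20,000 runs, simple randomisation, effects of 0.2, 0.5 and 1.0 SD) gave type I error of 0.053, 0.051 and 0.051, bias of about zero, and power of 0.78 to 0.79 at 0.4 SD. With an exact 48:48 split in each group, type I error was 0.048, 0.037 and 0.005. The test is then conservative.

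**5. Common cause under research question 3.** Let order be a 0/1 factor with variance 1/4 that shifts a utility by *dx* SDs and *b* by *dy* SDs. It adds *dx* × *dy*/4 to their correlation: 0.5 × 0.5/4 = 0.06, or 0.8 × 0.8/4 = 0.16. Shifts in opposite directions subtract the same amount. An order term in the regression removes this contribution.

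**The case against.** The strongest reply is that the plan is consistent as it stands. Randomising order is a recognised control at the design stage, and the article promises no analysis term for it. Clinician role is different: it is randomised partly so that its effect can be studied, and it is carried into the analysis for that reason. Covariate terms for nuisance factors are also commonly left to a full protocol or analysis plan that is not shown. All of this stands, so the point is an improvement and not an error. The article does, however, settle its tests and regressors, so the addition has a definite place to go.

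A reader might infer more than the document supports:

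- *That the patient-clinician comparison is biased or its P value unreliable.* Both groups receive the same randomisation, and step 4 shows no bias and no material excess of type I error.
- *That chance imbalance is an extra error.* Step 3 shows that the standard error already contains it.
- *That the power table is wrong.* It is in total-SD units and reproduces.
- *That the article undertakes to account for starting-point effects in the analysis.* The wording about accounting for effects concerns exercise and health-state order. For the starting point, the stated remedy is alternating presentation, with a random start added.
- *That dependence on the starting point will never be reported.* A condensed article's silence does not establish that.

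The power gain also matters less if the earlier result recurs. The earlier difference is 0.9/√((0.81 + 0.64)/2) = 1.06 SD, far above 0.4 SD.

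**Conclusion.** The point holds as a minor, near-free improvement. Two randomised factors that the design expects to matter are absent from the stated analyses of *b* and the utilities. The planned group comparison is valid without them. For a single factor, the gain at 0.4 SD is about 1 power point for a 0.3 SD effect and 2 to 3 points for 0.5 SD; only effects near 0.8 SD give 6 to 7 points. The analysis of *b* against the utilities has a slightly different reason for the change, because there exercise order could contribute to the association itself, by about 0.06 for two 0.5 SD shifts.

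Every effect size here is assumed. If the starting point acts differently in patients and clinicians, the unadjusted comparison estimates an average over starting points. That is still interpretable, and it is a reason to show the breakdown.

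**What to change.** - Keep the planned *t*, Mann-Whitney and Fisher tests. The last two do not take covariates and need no change.
- Add a prespecified linear model for *b* with group, exercise order and first-flipchart start (0 v 17 additional bleeds).
- Add exercise order to the comparisons of mean utilities, and exercise order and first-flipchart start to the regression of *b* on the utilities.
- Report *b* by starting point within each group, and the start-by-group interaction, as descriptive results.
- Do not adjust for the second-flipchart start (18 v 38). Only participants who accept 17 additional bleeds reach it, so it depends on the outcome.

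The cost is a few lines of analysis text and 2 of the 190 degrees of freedom (192 − 2) in the model for *b*. The assigned order and start must be kept in each participant's record. No extra participants or interview time are needed.
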